#### Allocation

Once obtaining a signed informed consent, each eligible participant would be randomized to omitting IMNI group or IMNI group (1:1) based on a computer-generated random number.

#### Treatment verification schedule

Daily alignment would be conducted by using skin markers for each participant. Online Cone-beam computed tomography (CBCT) was performed to verify the position with an action level of 5 mm for the first three fractions and weekly CBCT thereafter. In order to assure the quality of radiotherapy, the delineations and coverage requirement of CTV/PTV, and the dose constraints for OARs for the first 20 enrolled participants would be carefully checked by a senior radiation oncologist.

#### Data collection and management

By using an electronic data capture (EDC) system built by Ruijin hospital, all enrolled patients’ information would be collected and recorded, and only authorized and trained investigators would have the access to obtain these clinical data. If there is any amendments of the trial protocol, it should be reviewed and approved by the ethical committee of Ruijin hospital. Before the completion of the trial, auditing would be conducted every six months.

#### Follow up

After completion of radiotherapy, each enrolled patient would be followed up for at least 5 years. According to the follow-up program, the oncological outcomes and treatment-related complications will be assessed weekly during treatment and at each follow-up visit (1 month after RT, every 6 months after RT within 2 years; every 6 months for the first 5 years, and then annually) (Table 1). Any recurrence was cytologically or histologically confirmed whenever possible. According to the National Cancer Institute’s Common Terminology Criteria for Adverse Events version 3.0 (NCI-CTCAE 3.0) and the Radiation Therapy Oncology Group (RTOG) scale, acute and late radiation related toxicity during each follow-up visits would be recorded and graded.

**Table 1 Tab1:** shows the follow-up schedule

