**Methods:**

The IMNI PRECISION trial is a single institute, open-labeled, non-inferior, randomized controlled trial. A total of 214 clinically “high risk” BC patients which is characterized as having at least two of the five clinically adverse factors (age ≤ 40, three positive LN, T2 stage, grade 3 and Ki-67 index ≥ 14%), but genomic score “low risk” (the genomic score ≤ 44) N1 breast cancers are randomly assigned to omitting IMNI group (experimental group) or with IMNI (control group) with a 1:1 ratio. The primary endpoint of this trial is event-free survival, and secondary endpoints include overall survival and locoregional recurrence-free survival.

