Since IMNI would inevitably increase the lung and heart radiation dose, which might be related with an increased risk of developing cardiac or pulmonary toxicities [8]. Thus, in clinical practice, histological classification of breast tumors has been instrumental in determining a more personalized approach for pN1 breast cancer. Indeed, multiply studies have been performed to stratify clinical “high risk” early-stage BC patients who might be obtained from adjuvant post-mastectomy radiotherapy (PMRT) [9–14]. In consistent with those previous reports, our institution establishes and validates a prognostic nomogram including five risk factors (age, number of positive LN, tumor size, grade and Ki-67) accurately predict 5-year BC specific survival after mastectomy without adjuvant radiotherapy, which provides a practical stratification system to identify “high-risk” BC patients who might be indicated for adjuvant RT [15]. Subsequently, we validate this risk stratification model to individualize the adjuvant RT strategy among pT1-2N1 BC treated with modern systemic therapy, our result indicates that PMRT is an independent prognostic factor for DFS (HR 0.50, *p* = 0.05) among the clinical “high-risk” patients. However, those clinical “high-risk” patients could not benefit from comprehensive RNI with IMNI compared to those without IMNI (*p* > 0.05) [16]. In comparison with clinical risk model based on histopathologic factors, multi-genomic expression would provide individualized prognostic information for BC patients. Currently, multi-genomic expression profiling, such as 21-gene recurrence score and PAM-50-based 46-gene assay, has been recommended by international guidelines to tailor systemic therapy for patients with early-stage BC, but the clinical implications of multi-genomic expression for guiding radiotherapy is less well established. In a secondary analysis of a prospective trial of NSABP (National Surgical Adjuvant Breast and Bowel Project) B-14 and B-20,the authors find that the 21-gene Recurrence Score is an independent risk factor for locoregional recurrence in the cohort of 895 hormonal receptor (HR) positive patients treated with tamoxifen (HR2.16, 95%CI: 1.26–3.68, *p* = 0.005) [17]. In another retrospective analysis based on the Austrian Breast and Colorectal Cancer Study Group (ABCSG) 8 trial, the authors demonstrate that PAM-50 could be used to identify high local recurrence risk among postmenopausal HR-positive BC received with hormonal therapy, but it is not a predictive factor for obtaining from adjuvant RT [18]. RecurIndex, combined with 18 cancer genes and 10 reference genes, is a multigene profiling assay based on Chinese 28 genes, which could be used to predict the risk of local recurrence and distant metastasis for BC patients [19–22]. Our research team have demonstrated that the 5-year local–regional recurrence (LRR) free survival rates are 95–100% for N0 and N1 mastectomy BC patients with the 18-gene scores of < 44, while the LRR-free survival rate decreases to only 27–51% among BC patients with the 18-gene scores of more than 44 [23]. Thus, the 18-gene recurrence score might be used to identify biologically “high risk” breast cancer patients who would benefit from IMNI. Currently, to our best knowledge, there is no prospective studies to specifically investigate the role of IMNI in pN1 BC according to clinical-genomic model. As a result, we design this prospective trial by using an established clinical risk model combined with 28-gene score (RecurIndex) to individually stratify the risk of pN1 BC, and then to investigate whether those clinical “high-risk”, but genomic “low risk” pN1 BC patients would be safely omitting IMNI. Based on the Standard Protocol Items: Recommendations for Interventional Trials (SPIRIT) guidelines, our research team write the prospective trial protocol.

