The current trial has several potential limitations. First of all, this is a single institute randomized controlled trial, and enrolling patients are performed at our institution, which might limit generalization of the result to other medical centers. Secondly, this is an open-label trial, both the participants and radiation oncologists are aware of the study group assignment, which might increase the selection bias. Thirdly, the primary outcome is 2-year event-free survival, and the follow-up is too short for observing events. After completing the trial, long-term follow-up of enrolled participants would be continued. Fourthly, the randomization of the present trial does not stratify according to risk factors, which might another source of heterogeneity. Finally, the 10% non-inferiority margin between the two groups might be larger in clinical practice, although this margin is discussed and decided by our clinical team.

In conclusion, the IMNI PRECISION trial is a non-inferior, randomized controlled trial to compare the survival and toxicity differences of omitting IMNI vs delivering IMNI in pN1 BC patients by using our established clinical risk model and multi-genomic model. We anticipate that our results would provide high-level evidence to tailor IMNI according to individualized recurrence risk of BC.

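### Recorded toxicity is defined by its relation to radiation in an open-label trial, so the between-arm comparison of cardiac and pulmonary events may be biased in favour of omission

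*Protocol article*

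**What the plan says.** The Follow up section of the Protocol article describes toxicity collection twice, each time by cause. On assessment it says that "the oncological outcomes and treatment-related complications will be assessed weekly during treatment and at each follow-up visit". On recording it says that "acute and late radiation related toxicity during each follow-up visits would be recorded and graded", with "Common Terminology Criteria for Adverse Events version 3.0 (NCI-CTCAE 3.0) and the Radiation Therapy Oncology Group (RTOG) scale" as the grading systems.

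Three other statements bear on that rule:

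- The limitations in the Discussion say that "both the participants and radiation oncologists are aware of the study group assignment".
- The Background says that IMNI adds dose to the heart and lungs, "which might be related with an increased risk of developing cardiac or pulmonary toxicities".
- The closing paragraph of the Discussion describes the trial as one "to compare the survival and toxicity differences of omitting IMNI vs delivering IMNI in pN1 BC patients".

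Toxicity is not a listed endpoint. The Abstract states: "The primary endpoint of this trial is event-free survival, and secondary endpoints include overall survival and locoregional recurrence-free survival". The Outcomes section gives the same three.

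**The concern.** Whether an event is related to radiation is a judgement. Both arms receive chest wall or breast irradiation plus supra/infraclavicular irradiation, so the question arises in both. Exclusion criterion 12 shows that patients may have had adjuvant chemotherapy, a competing explanation for some cardiac and pulmonary findings. The judgement therefore has room to move, and the article itself supplies a direction: more heart and lung harm is expected with IMNI. If the person judging knows the arm, the same clinical event may more readily be called radiation related in the IMNI arm than in the omission arm.

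At stake is the benefit side of the trade-off. The Power and sample size calculation section sets 5-year event-free survival at 91% for control and 81% for omission, and the limitations concede that the 10% margin may be large. Avoided heart and lung toxicity is the reason the Background gives for questioning IMNI. A toxicity advantage that the collection rule could produce by itself would be weak support for accepting such a margin.

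**Working it through.** The article gives no toxicity rate, attribution rate or toxicity margin, so there is no figure to reproduce. The check is a comparison of passages, followed by an illustration on assumed rates.

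**Step 1. Passages side by side**

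| Question | Where | What the text gives |
|---|---|---|
| What is recorded and graded? | Follow up | Toxicity defined by its relation to radiation |
| Are other events excluded? | Follow up | Not stated |
| Who judges relatedness or grades? | Nowhere | Data collection and management covers only access: "only authorized and trained investigators would have the access to obtain these clinical data" |
| Is allocation known? | Discussion, limitations | Yes, to participants and radiation oncologists |
| Is a direction expected? | Background | Yes, more heart and lung harm with IMNI |
| Are arms to be compared on toxicity? | Discussion, conclusion | Yes |
| Are there measurements without an attribution step? | Table 1 | Yes, on a schedule not split by arm |

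Table 1 schedules echocardiography and ECG at baseline, 6, 12 and 18 months and yearly from 2 to 5 years. Myocardial enzymes follow the same schedule with an added 4-week test. Chest CT is at baseline, 12 months and yearly from 2 to 5 years.

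**Step 2. How the bias would arise**

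Let t be the true event rate, equal in both arms, and a the probability that an event is attributed to radiation, where attribution decides what is counted.

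- Recorded rate in an arm = t × a
- Spurious difference = t × (a for IMNI − a for omission)
- Spurious ratio = (a for IMNI) / (a for omission)

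If a is equal in both arms, the difference is 0 whatever t is.

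**Step 3. Illustration (all values of t and a are assumptions)**

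| t | a, IMNI | a, omission | Recorded, IMNI | Recorded, omission | Difference (points) | Ratio |
|---|---|---|---|---|---|---|
| 10% | 90% | 90% | 9.0% | 9.0% | 0 | 1.00 |
| 5% | 90% | 70% | 4.5% | 3.5% | 1 | 1.29 |
| 5% | 90% | 50% | 4.5% | 2.5% | 2 | 1.80 |
| 10% | 90% | 70% | 9.0% | 7.0% | 2 | 1.29 |
| 10% | 90% | 50% | 9.0% | 5.0% | 4 | 1.80 |
| 20% | 90% | 70% | 18.0% | 14.0% | 4 | 1.29 |
| 20% | 90% | 50% | 18.0% | 10.0% | 8 | 1.80 |
| 20% | 60% | 40% | 12.0% | 8.0% | 4 | 1.50 |
| 20% | 70% | 30% | 14.0% | 6.0% | 8 | 2.33 |

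With 214 / 2 = 107 patients per arm, 1 point is about 1 patient (107 × 0.01 = 1.07) and 8 points about 9 (107 × 0.08 = 8.56).

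**Step 4. What the illustration shows**

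The ratio depends only on the two attribution probabilities, so a rare event is distorted in ratio as much as a common one. The Background supports the direction of the bias. Nothing in the article supports a particular size.

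**The case against.** The strongest reply is that the recording sentence says what is graded and excludes nothing. The phrase about radiation may simply name the class of toxicity followed. The Data collection and management section says in general terms that information on all enrolled patients is captured electronically. This is also a condensed article: adverse-event definitions, the relatedness field and the case report form usually sit in the full protocol (Version 2.0, not shown), and such a field may already exist.

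Much of this stands. A reader might infer three stronger things that the documents do not support:

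- *Only events judged related are recorded.* The text contains no such restriction.
- *Unblinded radiation oncologists make the judgement.* The article says that they know the allocation. It does not say who attributes or grades.
- *Unattributed events never reach the database, so no analysis can repair the loss.* No passage says so. A fall in ejection fraction, an ECG change or a chest CT finding should also come to light through the Table 1 tests, which have no attribution step.

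Two further limits stand. Toxicity is not a listed endpoint, and the Statistical analysis section describes no test of it. Because both arms are irradiated, a large split in attribution cannot be presumed.

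The reply does not dispose of the point, because the criticism is of a rule the article states, not of detail it leaves out. Both sentences on toxicity are worded by cause, and no passage provides for cardiac and pulmonary events to be counted regardless of cause. The scheduled tests do not fully cover clinical events such as pneumonitis or a cardiac admission, and the article does not say that the toxicity comparison will rest on the tests.

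**Conclusion.** The concern holds as a risk, not as a demonstrated bias. Wording the recording rule by cause, in an open-label trial with a stated expectation about the very events of interest, lets knowledge of allocation influence which clinical cardiac and pulmonary events are counted. The announced toxicity comparison may then favour omission.

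This rests on two assumptions that the article neither confirms nor rules out: that relatedness decides what is counted, and that whoever judges it knows the arm. The size is unknown. The 1 to 8 points come wholly from assumed rates and fall to 0 if attribution is equal between arms.

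Event-free survival, overall survival and locoregional recurrence-free survival do not depend on this rule, so the non-inferiority conclusion is untouched. The point is of modest weight, but worth acting on because the remedy is cheap.

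**What to change.** In the Follow up section, state that:

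1. all cardiac and pulmonary adverse events, and all adverse events of grade 3 or higher, are recorded and graded regardless of attribution;
2. relatedness to radiation is held as a separate field and does not decide entry;
3. the toxicity comparison between arms uses all such events, supported by the echocardiography, ECG, myocardial enzyme and chest CT results already scheduled in Table 1.

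If the full protocol already works this way, one clarifying sentence is enough. Otherwise the cost is a wording change and a change to the electronic form, with no new visit or test. The downside is more adverse-event entries, some of them due to systemic therapy. At the article's status date 75 of 214 patients had been enrolled, so 214 − 75 = 139 were still to come and most of the collection lay ahead.

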	**STUDY PERIOD**									
	**Pre-radiotherapy**	**During Radiotherapy**	**Post-radiotherapy**							
**TIMEPOINT**	**0**	**Weekly**	**4w**	**6 m**	**12 m**	**18 m**	**2y**	**3y**	**4y**	**5y**
**ENROLLMENT:**										
Eligibility screening	X									
Informed consent	X									
Randomization	X									
**INTERVENTIONS:**										
Omitting IMNI		X								
With IMNI		X								
**ASSESSMENTS:**										
Physical Examination	X	X	X	X	X	X	X	X	X	X
Complete blood cell count	X	X	X	X	X	X	X	X	X	X
Thyroid function	X		X	X	X	X	X	X	X	X
Myocardial enzyme	X		X	X	X	X	X	X	X	X
Chest CT scan	X				X		X	X	X	X
Mammography					X		X	X	X	X
Ultrasound for Breast and regional nodes	X			X	X	X	X	X	X	X
ECG	X			X	X	X	X	X	X	X
Echocardiography	X			X	X	X	X	X	X	X

### Statistical analysis

Data will be analyzed in the “intention to treat” participants cohort. For the primary endpoint, Kaplan–Meier (K-M) analysis will be conducted to compare the EFS differences between omitting IMNI and with IMNI groups. Regarding the secondary outcomes of overall survival and locoregional recurrence free survival, K-M analysis and log-rank test would be performed. Descript analysis was used to summarize the baseline characteristics. Continuous variables were summarized by median and range, and qualitative variables were described as frequencies and proportion.

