#### Power and sample size calculation

The power and sample size are calculated according to the hypothesis that the 5-year event-free survival of omitting IMNI group is non-inferior to those patients treated with comprehensive RNI with IMNI. According to survival outcome of pN1 breast cancer in our institute, the 5-year event free survival (EFS) is estimated to be 91% for the control and 81% for experimental groups, respectively. The permissible limit for HR is 2.30, with statistical power of 80%, an alpha level of 0.025 (one-sided). With an anticipated enrolment period of 24 months, a total sample size of 208 patients is estimated to be needed. To compensate for eligible patients, the targeted number of patients is set at 214.

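### The stated primary analysis is a Kaplan-Meier comparison of EFS that does not carry over the non-inferiority limit and one-sided alpha, and the limit itself is given in two forms

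*Protocol article*

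**What the plan says.** All references are to the protocol article.

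- **Power and sample size calculation.** The hypothesis is that "the 5-year event-free survival of omitting IMNI group is non-inferior to those patients treated with comprehensive RNI with IMNI". The design figures follow: "the 5-year event free survival (EFS) is estimated to be 91% for the control and 81% for experimental groups"; then "The permissible limit for HR is 2.30, with statistical power of 80%, an alpha level of 0.025 (one-sided"; then "With an anticipated enrolment period of 24 months, a total sample size of 208 patients is estimated to be needed". After an allowance, "the targeted number of patients is set at 214".
- **Statistical analysis.** In the intention-to-treat cohort, the primary endpoint gets a Kaplan-Meier analysis: "analysis will be conducted to compare the EFS differences between omitting IMNI and with IMNI groups". For overall survival and locoregional recurrence-free survival, "K-M analysis and log-rank test would be performed". No effect measure, confidence limit, margin or decision rule is attached to EFS.
- **Discussion, limitations paragraph.** The margin appears on an absolute scale: "the 10% non-inferiority margin between the two groups might be larger in clinical practice". The same paragraph describes the primary outcome as EFS at 2 years, whereas Participants and the sample size section use 5 years.

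**The concern.** A non-inferiority conclusion needs three things: an effect measure, a margin on that measure's scale, and a confidence limit (or equivalent shifted test) to set against the margin. The sample size section supplies a margin and an alpha. The analysis section supplies a method and mentions neither, and Kaplan-Meier curves alone decide nothing against a margin.

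A reader cannot repair this by going back to the sample size section, because the article gives the margin on two scales and the endpoint at two times. Whoever writes the final analysis would have to choose, possibly after seeing the data, and the choice changes both the error rate and the power.

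There is also a risk of misreading. When a non-inferiority trial's analysis is described only as comparing differences, a non-significant result is easily taken as support for the new strategy. The Background already reports an earlier institutional comparison of IMNI with no IMNI as showing no benefit on the strength of p > 0.05.

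**Working it through.** **Inputs.** Control 5-year EFS 91%, experimental 81%, HR limit 2.30, one-sided alpha 0.025, power 80%, 24-month accrual, 208 patients raised to 214 (sample size section); 1:1 allocation (Trial design); at least 5 years' follow-up (Follow up); 10% margin and 2-year EFS (Discussion). Assumed here: exponential EFS, uniform accrual, no dropout.

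**1. The plan's own figure.** Events for an HR limit of 2.30 (Schoenfeld): 4 × (1.960 + 0.842)² / (ln 2.30)² = 45.3, so 46. With 91% and 81% EFS, 2-year accrual and 5 further years, the mean event probability is 0.165, and 46 / 0.165 gives 279 patients. With both arms at 91% the probability is 0.107, giving 431. A 10-point risk-difference margin at 91% in both arms needs 258. None of these gives 208. That is a separate matter and does not decide this point, but it means the sample size does not reveal which rule was intended.

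**2. Are the two margins the same rule?**
- 91% versus 81%: HR = ln 0.81 / ln 0.91 = 2.23.
- HR 2.30 from 91%: 0.91^2.30 = 0.805, a difference of 10.5 points.

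At 5 years they are close but not identical. At 2 years they separate. Control EFS would be 0.91^(2/5) = 0.963. HR 2.30 then gives 0.963^2.30 = 0.917, a 4.6-point difference, whereas a 10-point margin gives 0.863, or HR = ln 0.863 / ln 0.963 = 3.9. So the time point matters as well as the scale.

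**3. What if non-significance were taken as success?** This rule is hypothetical; the article does not state it. Trials of 214 patients were simulated with control hazard −ln(0.91)/5 = 0.01886 per year (10,000 runs per scenario in the main runs). Ranges cover repeated simulations with exactly 5 years' follow-up or with 5-7 years.

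| Truth | Two-sided 5% log-rank non-significant | Upper 95% limit of HR below 2.30 | Upper 95% limit of 5-year difference below 10 points |
|---|---|---|---|
| HR 2.30 | about 31-40% | about 2.5-3% | about 2-2.5% |
| 91% vs 81% (HR 2.23) | about 36-44% | about 3% | about 2.6% |

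At the HR limit, either confidence-limit rule keeps close to the planned 2.5%. The hypothetical reading gives 31/2.5 to 40/2.5, roughly 12 to 16 times that.

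**4. Power of each proper rule if the arms are truly equal at 91%.**
- HR rule: expected events are 214 × 0.09 = 19.3 (exactly 5 years) or 214 × 0.107 = 22.9 (5-7 years). Power = Φ(√d / 2 × ln 2.30 − 1.960). For d = 19.3: Φ(1.828 − 1.960) = 0.45. For d = 22.9: Φ(1.992 − 1.960) = 0.51. Across formula and simulation the range is about 43-52%.
- 10-point rule at 5 years: standard error = √(2 × 0.91 × 0.09 / 107) = 0.0391. Power = Φ(0.10 / 0.0391 − 1.960) = Φ(0.596) = 0.72. Across formula and simulation the range is about 71-73%.

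So the unstated choice of scale moves power by more than 20 percentage points, and both rules fall short of 80%.

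**The case against.** The strongest reply is that the criterion exists. The sample size section states the hypothesis, the HR limit and the alpha, and the trial is called non-inferior throughout. The article condenses a full protocol (Version 2.0) that is not shown, and an analysis plan may exist; estimator, model and confidence-limit rule are commonly left to those. Nor is Kaplan-Meier the wrong tool. It is an estimation method with no null hypothesis of its own, and a 5-year Kaplan-Meier difference whose confidence limit is set against a margin is a valid non-inferiority analysis. The stated sentence is compatible with that.

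Much of this stands. The method is incomplete rather than necessarily wrong, and the unseen documents may complete it. What does not fall away is that the published primary analysis is not tied to the published limit, and that the article contradicts itself on the margin's scale and on the time point. Those conflicts are in the text and are not detail left to another document.

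Two stronger readings are tempting and are not supported:

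- A reader might infer that the trial will treat a non-significant EFS difference as proof that omission is safe. The article states no such rule, and it names the log-rank test only for the secondary endpoints. The 31-40% is therefore the size of a risk, not an error rate of the stated plan.
- A reader might add that a log-rank test would be non-significant in about 52% of trials at a true HR of 2.0. That is not false reassurance by the protocol's own standard, because 2.0 lies inside the 2.30 limit.

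**Conclusion.** The point holds in a limited form. As published, the primary analysis does not test the non-inferiority hypothesis, because neither the HR limit of 2.30 nor the one-sided 0.025 is carried into it. The criterion cannot be recovered with certainty, since the margin is HR 2.30 in one place and 10% in another (91% versus 81% implies HR 2.23) and the endpoint is at 5 years in one place and 2 years in another.

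If the gap were filled by a non-significance reading, omission would be endorsed in about 31-40% of trials at a true HR of 2.30, against the planned 2.5%. If it is filled properly, power at equal arms is about 43-52% or 71-73%, depending on the scale chosen. These figures assume exponential EFS, 91% control EFS at 5 years, 214 patients, 5 to 7 years of follow-up and no dropout; dropout would lower the power. The gap bears on the trial's sole primary conclusion and should be closed, with the reservation that the full protocol or an analysis plan may already do so.

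**What to change.** Before outcome data mature and without sight of results by arm:

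1. Choose one margin scale and one time point, state them in the Statistical analysis section, and reconcile the sample size section and the Discussion with that choice.
2. Add the decision rule: non-inferiority is concluded only if the upper limit of the two-sided 95% CI is below the margin, using either the Cox EFS hazard ratio (omission versus IMNI) against the HR limit, or the 5-year Kaplan-Meier EFS difference (IMNI minus omission) against the absolute margin.
3. Report the other measure with its CI as supportive.
4. State that a non-significant difference is not evidence of non-inferiority.
5. Disclose the power of the chosen rule at 214 patients: about 43-52% for HR 2.30 or about 71-73% for 10 points at 5 years, if both arms are truly at 91%.

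The cost is a protocol amendment in wording, with ethics committee approval as the article requires, and no new data. Current trial status reports 75 patients enrolled by 30 July 2022, so at that date the rule could still be fixed early. The real price is the disclosure: either rule shows that the planned size does not deliver 80% power when the arms are equal at 91%, and wording cannot cure that.

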## Methods

### Trial design

This is a prospective, non-inferiority, open-labeled, randomized controlled trial. We recruit histo-pathologically confirmed invasive breast cancer patient with pT1-2N1 after curative surgery from Ruijin Hospital, Shanghai Jiaotong university school of medicine. We initially use the clinical model to identify the clinically “high risk” of developing recurrence BC patients, defining as having at least two of the five clinical risk factors (age ≤ 40, three positive LN, T2 stage, grade 3 and Ki-67 index ≥ 14%). The formalin-fixed and paraffin-embedded (FFPE) tumor samples of those clinically “high-risk” BC would be detected using RecurIndex test, which is a multi-genomic test established according to Chinese 28 genes [19, 20]. Based on previous research, the accuracy of RecurIndex for predicting local–regional recurrence (LRR) in BC patients could be up to 93% by using 44 score as the threshold value for high or low risk. Therefore, patients with score ≤ 44 are classified as genomic low risk, > 44 are regarded as genomic high risk [23]. For early-stage BC patients with clinically “high risk” and genomic high risk, CW/WB + comprehensive RNI with IMNI would be recommended. For early-stage BC patients with clinically “high risk” but genomic low risk, these patients will be randomly assigned to RNI omitting IMNI (experimental group) or RNI with IMNI group (controlled group) with a 1:1 allocation ratio. Randomization was conducted with computer-generated random number by using SPSS software version 21.0 (IBM Corporation, Armonk, NY, USA). Participants will be followed until death or drop out of the study. Figure 1 shows the design of the IMNI PRECISION trial.

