### Outcomes

#### The primary outcomes

The primary outcome is the event-free survival, which is determined as the time from randomization to the time of a first recurrence in ipsilateral chest wall or in breast or in regional nodal or distant sites, a contralateral BC, or breast cancer specific death.

The secondary endpoints include the following outcomes: (1) local regional recurrence free survival, which is defined as the time from randomization to a first recurrence in ipsilateral chest wall or in breast or in regional nodal areas. (2) overall survival which is defined as the time from randomization to death from any cause.

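### Locoregional recurrence-free survival does not count death as an event but is to be estimated by Kaplan-Meier, which slightly overstates the proportion of patients with locoregional recurrence

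*Protocol article*

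**What the plan says.** The secondary endpoints are defined in the protocol article under The primary outcomes. Locoregional recurrence-free survival is "the time from randomization to a first recurrence in ipsilateral chest wall or in breast or in regional nodal areas". Neither death nor distant relapse is on that list. The same section treats the other two endpoints differently. Event-free survival also takes in relapse at distant sites, cancer in the other breast and death from breast cancer, and overall survival counts death from any cause.

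The Statistical analysis section then fixes the method: "Regarding the secondary outcomes of overall survival and locoregional recurrence free survival, K-M analysis and log-rank test would be performed". It names no competing-risk method for the locoregional endpoint.

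Two statements bear on how long patients are observed for it. Trial design says "Participants will be followed until death or drop out of the study", and Follow up says "each enrolled patient would be followed up for at least 5 years". The follow-up schedule lists physical examination and ultrasound of the breast and regional nodes up to 5 years, with no stop at distant relapse.

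**The concern.** The endpoint and the estimator do not fit each other. Kaplan-Meier treats a censored patient as someone who could still have the event later, at the same rate as those still under observation. That is reasonable for a patient whose follow-up has simply ended, but not for one who has died. One minus Kaplan-Meier then describes locoregional risk in a hypothetical population in which nobody dies, and it is at least as large as the proportion of patients who actually relapse locoregionally.

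Locoregional recurrence is the outcome most directly tied to leaving out a nodal volume, so readers are likely to take the reported percentage in each arm as an absolute risk. What is at stake is that percentage and its interval. The test between arms is not affected.

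**Working it through.** The article gives no rate, power or sample size for locoregional recurrence-free survival, so there is no figure of its own to reproduce. The check asks how far one minus Kaplan-Meier departs from the cumulative incidence at plausible rates.

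**Inputs**
- Locoregional recurrence at 5 years, L. Background reports, for genomic low risk, that "free survival rates are 95–100% for N0 and N1 mastectomy BC patients with the 18-gene scores of < 44", which is 0-5% recurrence. I take L = 5%, the upper end.
- Death without prior locoregional recurrence by 5 years, D. The article gives no figure. I assume 2%, 5% and 10%.
- Event-free survival, used only for an upper bound: "the 5-year event free survival (EFS) is estimated to be 91% for the control and 81% for experimental groups" (Power and sample size calculation).
- Patients per arm: 214/2 = 107.

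**Formulas** (constant hazards assumed)
- Locoregional hazard a = -ln(1 - L)/5; competing hazard b = -ln(1 - D)/5.
- One minus Kaplan-Meier at 5 years = 1 - exp(-5a) = L.
- Cumulative incidence at 5 years = a/(a + b) × [1 - exp(-5(a + b))] = a/(a + b) × [1 - (1 - L)(1 - D)].

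**Death as the only competing event, L = 5%** (5a = 0.0513)
- D = 2% (5b = 0.0202): 0.0513/0.0715 × (1 - 0.95 × 0.98) = 0.717 × 0.0690 = 4.95%. Overstatement 0.05 point.
- D = 5% (5b = 0.0513): 0.5 × (1 - 0.95 × 0.95) = 0.5 × 0.0975 = 4.88%. Overstatement 0.13 point.
- D = 10% (5b = 0.1054): 0.0513/0.1567 × (1 - 0.95 × 0.90) = 0.327 × 0.145 = 4.75%. Overstatement 0.25 point.

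In a 107-patient arm, 0.13 point is about 0.14 of a patient and 0.25 point about 0.27 of a patient.

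**Upper bound: every other event-free-survival event also ends locoregional observation.** Let s be the share of those events that is locoregional. One minus Kaplan-Meier is then 1 - EFS^s, and the cumulative incidence is s × (1 - EFS).
- EFS 81%, s = 0.5: 1 - 0.81^0.5 = 10.00%, against 0.5 × 19% = 9.50%. Overstatement 0.50 point. Over s = 0.1 to 0.7 the range is 0.19-0.50 point.
- EFS 91%, s = 0.5: 1 - 0.91^0.5 = 4.61%, against 0.5 × 9% = 4.50%. Overstatement 0.11 point. Over the same range of s it is 0.04-0.11 point.

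The 0.50-point case has 10% locoregional recurrence, above the range in Background. With L = 5% at 81% event-free survival, 5a/(5a + 5b) = 0.0513/0.2107 = 0.243. The cumulative incidence is 0.243 × 19% = 4.62%, an overstatement of 0.38 point.

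**Scale.** The standard error of a difference between two 5% proportions with 107 patients each is sqrt(2 × 0.05 × 0.95/107) = 2.98 points.

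**The case against.** The strongest objection is materiality. On the one competing event that is certain, the error is a fraction of one patient per arm and less than a tenth of the standard error of the arm difference (0.25/2.98 = 0.08). It touches no primary conclusion, test or sample size. This stands, and it sets the weight of the point.

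A second objection is that this is a condensed article, and that censoring rules for a secondary endpoint belong in the analysis plan. That is fair for details such as how a locoregional recurrence after distant relapse is counted, and I raise no finding on that. It does not dispose of the main point, because the article itself states both the event definition and the estimator. A related objection is that the article never says one minus Kaplan-Meier will be presented as absolute risk. That is also true, but a Kaplan-Meier percentage for a recurrence endpoint is ordinarily read that way.

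Three stronger readings are tempting, and the document does not support them.
- *Distant relapse competes as well.* A reader might infer this because it is not an event for the endpoint. But a patient with distant relapse can still relapse locoregionally, follow-up runs to death or drop-out, and the schedule continues nodal ultrasound without a stop at distant relapse. Contralateral cancer, also an event-free-survival event, need not compete either.
- *The bias is larger in the omission arm.* A reader might infer this from the 91% and 81% in the sample-size section. The text there calls them estimates, but the limitations paragraph of the Discussion describes the 10-point gap as the non-inferiority margin. On that reading 81% is the limit to be excluded, and similar arms are the working assumption. With equal event rates in the two arms, the difference between them is not biased.
- *The error becomes substantial at 10 years.* It does grow with time, and follow-up continues past 5 years, but no 10-year locoregional analysis is specified.

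**Conclusion.** The point holds and is minor. As defined and analysed in the article, locoregional recurrence-free survival will overstate the proportion of patients with locoregional recurrence wherever patients die without it. The direction is certain. The size at 5 years is about 0.05-0.25 percentage points, assuming constant hazards, 5% locoregional recurrence and 2-10% death. It could approach 0.5 point at 81% event-free survival only if locoregional observation ended at distant relapse and the other event-free-survival events, which the article does not say. The overstatement would differ between arms only if competing-event rates did, and which arm would have more cannot be told in advance. The log-rank comparison of cause-specific hazards is sound as planned, and Kaplan-Meier is right for overall survival.

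**What to change.** In the Statistical analysis section, state that locoregional recurrence will be reported by the cumulative incidence function (Aalen-Johansen estimator) with death as a competing event. Keep the log-rank test and describe it as the comparison of cause-specific hazards.

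Alternatively, change the definition in the Outcomes section so that death counts as an event. The endpoint then matches its name, and Kaplan-Meier is appropriate. The price is that it no longer isolates locoregional failure, so the first option suits the trial's question better.

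Either change takes about one sentence and needs no extra patients, visits or data, since deaths are already collected for overall survival. With the first option, the visible effect is a slightly lower locoregional percentage.
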